### **Methods for additional analyses (e.g. subgroup analyses)**

We will conduct a subgroup analysis for participants that use contact lenses. We hypothesize that the effect may be smaller for this group, since one possible mechanism for viral transmission is that the viruses attach to ACE-2 receptors in the cornea, which we assume are protected by contact lenses (2).

We may also conduct subgroup analyses for groups with different vaccination status (number of vaccinations), and for groups that have or have not had COVID-19 previously.

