Many have easy access to sunglasses, and it requires little effort to use them in everyday life - after all, some of them are worn just for fashion. Repurposing sunglasses for infection control could be a simple, readily available, environmentally friendly, safe, and sustainable infection prevention measure. Those who regularly use contact lenses could forego using lenses for infection control reasons and wear the eyeglasses they typically have, instead. Again, this could be a very simple measure to prevent infections. We therefore plan to carry out a randomized trial in the community, to assess whether wearing glasses reduces the risk of SARS-CoV-2 infection.

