### Strategies to improve adherence to interventions

None. We do not plan to maintain any form of contact with the participants between trial enrollment and data collection, 3 days after the 2-week trial period.

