### Outcomes

Day 1 of trial period is the first day the individual participates in the trial. The intervention group will be asked to wear glasses until day 14. Three days later (day 17), the participants will complete an online questionnaire.

The primary outcome is

- positive COVID-19 test result registered in public registry (from day 3 to day 17; MSIS database).

Secondary outcomes are

- health care use for respiratory symptoms (from day 3 to day 28; KPR and NPR databases)
- health care use for injuries (from day 1 to day 21; KPR and NPR databases)
- health care use (all causes) from day 1 to day 21 (data source: KPR and NPR databases)
- any positive COVID-19 test result (from day 1 to day 17; self report)
- respiratory symptoms from day 1 to day 17 (self report)
- health care use for respiratory symptoms (from day 1 to day 17; self report)
- health care use for injuries (from day 1 to day 17; self report)
- health care use (all causes) (from day 1 to day 17; self report)

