## Data collection and management

### Plans for assessment and collection of outcomes

Our outcome data will be collected from national registries and from a questionnaire that the participants will be asked to complete 3 days after their trial period.

From national registries we will collect the following data:

- COVID-19 test (YES/NO) (MSIS-database)
- Result of COVID-19 test (POSITIVE/NEGATIVE) (MSIS-database)
- Health care utilization (KPR and NPR databases)
- COVID-19 vaccination status (SYSVAK).

- Age (Population registry)
- Gender (Population registry)

The questionnaire includes the following questions:

- Regular use of contact lenses?
- Use of glasses outside, in public spaces during study period? (all the time; most of the time; some of the time; never)
- Use of health care services?

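### Contact-lens use, which defines the only firmly planned subgroup, is recorded only on day 17 and only for questionnaire responders; it should be asked before allocation is shown

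*Protocol*

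**What the plan says.** The protocol's section on additional analyses makes one firm commitment: "We will conduct a subgroup analysis for participants that use contact lenses". The direction is stated in advance: "We hypothesize that the effect may be smaller for this group". The other subgroups are optional: "We may also conduct subgroup analyses for groups with different vaccination status", and likewise for previous COVID-19.

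Lens use appears in one place only, the data-collection section, as the item "Regular use of contact lenses" in "a questionnaire that the participants will be asked to complete 3 days after their trial period". The Outcomes section fixes the timing: "Three days later (day 17), the participants will complete an online questionnaire". Table 1 shows eligibility, consent and allocation on Day 1 and no baseline question on lenses. The register variables (age, gender, vaccination, test results, health care) do not include lens use. The eligibility section admits lens users without describing any record of who they are. No later contact fills the gap: "We do not plan to maintain any form of contact with the participants between trial enrollment and data collection".

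The Outcomes section takes the primary outcome from the MSIS registry. The protocol allows up to two questionnaire reminders, gives no expected response rate, and plans no method for missing data.

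**The concern.** A subgroup analysis keeps the protection of randomisation when membership is fixed before allocation and known for everyone randomised. Here neither is secured.

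- **Responders only.** The primary outcome is available without the questionnaire, but subgroup membership is not. Participants know their arm, and by day 17 many may know their test result, so returning the form may depend on both.
- **The answer may depend on allocation.** The intervention allows any type of glasses, and the Background raises the option that "Those who regularly use contact lenses could forego using lenses for infection control reasons and wear the eyeglasses they typically have, instead". Controls are encouraged not to wear glasses near others. A lens user in the glasses arm who switched might answer no on day 17, where a similar control answers yes.

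At stake is how the one committed subgroup can be read. If no baseline value is collected, no later analysis can recover it.

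**Working it through.** **1. The plan's own figure.** Inputs from the Sample size section: control risk 2%, relative reduction 25% (so 1.5%), p < 0.05 (taken as two-sided), power 80%, 1:1.

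n per arm = [1.960·√(2·0.0175·0.9825) + 0.8416·√(0.02·0.98 + 0.015·0.985)]² / 0.005² = 10,795, or 21,590 in total. The stated figure of around 22,000 is reproduced. The point does not depend on it; it only sets the scale below.

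**2. Precision lost by restricting to responders.** The lens-user share and response rate are assumptions; the protocol gives neither.

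| Lens share of 22,000 | Response | Lens users analysed | Power for 2.0% v 1.5% |
|---|---|---|---|
| 20% | 100% | 4,400 | 24% |
| 20% | 80% | 3,520 | 20% |
| 10% | 100% | 2,200 | 14% |
| 10% | 80% | 1,760 | 12% |

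**3. Selective response.** Within lens users, the risk among responders in an arm equals the true risk × (response among the infected ÷ overall response in that arm). So the observed RR equals the true RR × (that quotient in the glasses arm ÷ that quotient in controls). There is no bias if the quotients match. If they differ, the bias can go either way, and nothing in the protocol says which.

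**4. Classification affected by allocation.** Illustration with assumed inputs: 20% lens users, 70% adherence, RR 0.75 in wearers and 1.00 in non-wearers, control answers unaffected. The true RR is 1 − 0.25·0.7 = 0.825 with and without lenses. Let m be the share of adherent glasses-arm lens users who answer no.

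- Adherent share among those answering yes: 0.7(1−m) / [0.7(1−m) + 0.3]
- Adherent share among those answering no: (0.8·0.7 + 0.2·0.7·m) / (0.8 + 0.2·0.7·m)
- Observed RR in each group: 1 − 0.25 × adherent share
- Apparent lens share in the glasses arm: 0.2 − 0.2·0.7·m

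| m | RR, lens | RR, no lens | Ratio | Apparent lens share, glasses arm (controls 20%) |
|---|---|---|---|---|
| 0 | 0.825 | 0.825 | 1.00 | 20% |
| 25% | 0.841 | 0.822 | 1.02 | 16.5% |
| 50% | 0.865 | 0.819 | 1.06 | 13% |

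A second set of assumptions fixes the true RR in lens users at 0.75 and lets adherence a run from 50% to 90%. The RR in adherers is then 1 − 0.25/a. With 10% to 50% of adherers answering no, the observed RR lies between 0.75 and 0.83.

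**5. Against sampling error.** With 20% lens users of 22,000 there are 2,200 lens users and 8,800 others per arm. Expected events (control, glasses at RR 0.825) are 44 and 36.3, and 176 and 145.2.

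- Variance of log RR, lens: 1/44 + 1/36.3 − 2/2,200 = 0.0494
- Variance of log RR, others: 1/176 + 1/145.2 − 2/8,800 = 0.0123
- SE of the log ratio: √0.0617 = 0.25

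The artefact on the log scale is about 0.02 to 0.055, or roughly 0.1 to 0.2 standard errors.

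**The case against.** The strongest reply is that the item measures a habit. It asks about regular use and gives no time frame, while the next item, on wearing glasses, is expressly limited to the study period. The eligibility section describes the same people by what they typically use. Someone who left lenses out in some settings for two weeks could still answer yes, and then step 4 gives no shift. This stands, although the wording does not settle which period is meant.

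A reader might infer that the protocol expects lens users to leave their lenses out. It does not: the Background says only that they could, as a possible public measure, and sunglasses over lenses satisfy the intervention. The values of m above therefore have no basis in the document.

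A reader might also fault the plan for naming no interaction test. The protocol speaks of a subgroup analysis and states a comparative hypothesis, and the choice of test is commonly left to the SAP, so this is no fault here.

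Finally, this is a low-powered secondary analysis. That limits the severity. It does not answer the responder restriction, or the fact that an uncollected baseline value cannot be recovered.

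**Conclusion.** The point holds as a weakness in data collection for a secondary analysis. The text establishes that the defining variable of the only committed subgroup is collected after an open intervention and only from responders, while the primary outcome needs no questionnaire.

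It is tempting to conclude that the subgroup is biased toward the stated hypothesis. The document does not support that. The shift requires that lens users switch, that they read the item as use during the trial, and that glasses have an effect (or that adherers differ in baseline risk). Selective response can push either way. Under the assumed inputs the artefact is a ratio of 1.02 to 1.06, small beside the subgroup's imprecision, and it is nil if answers reflect habitual use. The loss of power at 80% response is also modest (24% to 20%, or 14% to 12%).

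The primary intention-to-treat analysis is unaffected. Severity is low to moderate. The case for acting is that the remedy is nearly free and cannot be applied retrospectively.

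**What to change.** Ask habitual contact-lens use on the Nettskjema enrolment form, before allocation is displayed. Add the item to the Day 1 column of Table 1. Define the subgroup from that answer for all randomised participants, so that the registry outcome can be analysed whether or not the day-17 form is returned.

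If enrolment has already started, reword the day-17 item to ask about habitual use before day 1, and label the subgroup analysis exploratory. This reduces misclassification but leaves the restriction to responders.

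The cost is one extra item at enrolment and a short protocol edit, with no added contacts, staff or participants.

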#### **Methods in analysis to handle protocol non-adherence and any statistical methods to handle missing data**

We will include all data collected, and it will be analyzed by the intention to treat principle. We do not plan to use any methods for handling missing data.

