|------------------------------------------------------------------------------------------------------------------|--|---|----|
| symptoms)                                                                                                        |  |   |    |
| Need for medical care (due to injuries)                                                                          |  | X | X  |
| Participant characteristics (registers)                                                                   |  |   |    |
| Age, gender, vaccination status, notified test results (COVID-19), registered medical care/admission to hospital |  |   | X* |

\* Data on vaccination status and notified COVID-19 test results, will also be collected for the pre-study period

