## **Statistical methods**

### **Statistical methods for primary and secondary outcomes**

We will conduct conventional unadjusted analyses to estimate the relative risk for the prespecified outcomes, with 95% confidence intervals. The primary analysis will follow the intention-to-treat (ITT) principle (patients will be analyzed according to their group allocation).

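### Five questionnaire-based secondary outcomes will be compared among responders only, with missing-data methods ruled out, although linked registry data could describe the non-responders

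*Protocol*

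**What the plan says.** The protocol's Outcomes section takes the primary outcome from a registry: "positive COVID-19 test result registered in public registry (from day 3 to day 17; MSIS database"). It then lists eight secondary outcomes. Three come from the KPR and NPR registries, for example "health care use for respiratory symptoms (from day 3 to day 28; KPR and NPR databases"). Five are self-reported on day 17: any positive test, respiratory symptoms, and health care use for respiratory symptoms, for injuries and for all causes. The symptom item reads "respiratory symptoms from day 1 to day 17 (self report").

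The analysis is fixed in two places. The section on statistical methods gives one rule for every outcome: "We will conduct conventional unadjusted analyses to estimate the relative risk for the prespecified outcomes, with 95% confidence intervals". Under the section on non-adherence and missing data: "We will include all data collected, and it will be analyzed by the intention to treat principle", followed directly by "We do not plan to use any methods for handling missing data".

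On follow-up, the section on adherence says "We do not plan to maintain any form of contact with the participants between trial enrollment and data collection". The section on retention allows up to two reminders to those who have not withdrawn and have not returned a completed form. Only the data analysts are blinded.

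Consent at enrolment covers national registers as well as questionnaires. Table 1 (Participant timeline) lists what the registers supply: "Age, gender, vaccination status, notified test results (COVID-19), registered medical care/admission to hospital". Its footnote extends vaccination status and notified test results to the period before the study.

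**The concern.** The missing-data sentence is a decision, not a detail left for a later document; an analysis plan that followed it would contain no such method. For the five self-reported outcomes, the data collected are the responders' data, so each relative risk compares those who answered in one arm with those who answered in the other. Participants know their arm, and whether someone answers on day 17 may depend both on that and on having been ill. If the two act together, a relative risk away from 1 can arise with no effect of glasses.

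This trial is unusually well placed to do better. Registry data on age, sex, vaccination, earlier tests, test results during the trial and health care contacts are available for participants who never return the form, provided they have not withdrawn. The stated rule leaves that information unused.

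**Working it through.** **The protocol's own figure.** The Sample size section gives 2% control risk, a 25% relative reduction (so 1.5%), p < 0.05 and 80% power, and states about 22,000 participants. Taking the test as two-sided, with pooled variance under the null:

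n per arm = [1.960·√(2·0.0175·0.9825) + 0.842·√(0.02·0.98 + 0.015·0.985)]² / 0.005² = 10,795, or 21,590 in total.

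The figure reproduces (22,384 with continuity correction). The 2% risk and the target relative risk of 0.75 serve as yardsticks below.

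**Inputs for the bias check**
- From the protocol: risk p = 0.02; 25,000 randomised 1:1 (Abstract), so 12,500 per arm.
- Assumed, because the protocol gives no response rate: 80% response in everyone except glasses-arm participants with the event, whose rate r is varied. No true effect.
- Assumed for a commoner outcome such as respiratory symptoms: p = 0.30.

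**Formula.** Risk among responders = p·r / [p·r + (1−p)·0.80]. In the control arm, where r = 0.80, this equals p.

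**Results at p = 0.02**
- r = 0.70: 0.014 / (0.014 + 0.784) = 1.754%; RR = 1.754 / 2 = 0.88.
- r = 0.60: 0.012 / (0.012 + 0.784) = 1.508%; RR = 0.75.
- r = 0.90: 0.018 / (0.018 + 0.784) = 2.244%; RR = 1.12, so the bias can run either way.
- Events respond at 70% in both arms: both risks are 1.754%; RR = 1.00.
- 70% response in one arm and 90% in the other, unrelated to outcome: RR = 1.00.

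With 12,500 per arm and a two-sided 5% test, the chance of a false positive is about 25% at r = 0.70 and 76% at r = 0.60.

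**Results at p = 0.30**
- r = 0.70: 0.21 / (0.21 + 0.56) = 27.3%; RR = 0.91, false-positive chance about 99%.
- r = 0.60: 0.18 / (0.18 + 0.56) = 24.3%; RR = 0.81, false-positive chance close to 100%.

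The relative bias is slightly smaller for a common outcome, but with so many events it is far more likely to reach significance.

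**What registry data would recover.** Suppose the registry holds a share s of true cases and no false ones, and the analysis conditions on registry status. The estimated glasses-arm risk is then

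s·p + (1 − s·p) · p(1−s)r / [p(1−s)r + (1−p)·0.80].

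For r = 0.70 and s = 0.3: 0.006 + 0.994 · 0.0098 / (0.0098 + 0.784) = 0.01827; RR = 0.914. In full, at p = 0.02:

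| Response in glasses-arm cases | Responders only | s = 30% | s = 50% | s = 80% |
|---|---|---|---|---|
| 70% | 0.88 | 0.91 | 0.94 | 0.98 |
| 60% | 0.75 | 0.83 | 0.88 | 0.95 |

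The share s is also an assumption. At s = 30%, about 70% of the bias remains: (1 − 0.827) / (1 − 0.754) = 0.70.

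**Registry counterparts**

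| Self-reported, day 1–17 | Registry counterpart |
|---|---|
| Any positive test | MSIS, day 3–17 (primary) |
| Respiratory health care use | KPR/NPR, day 3–28 |
| Injury health care use | KPR/NPR, day 1–21 |
| All-cause health care use | KPR/NPR, day 1–21 |
| Respiratory symptoms | None; respiratory health care use is only an indirect proxy |

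**The case against.** Most of what can be said on the other side concerns weight, and much of it stands.

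- The design already protects most of the ground. Four of the five outcomes are mirrored by registry outcomes that do not depend on the questionnaire. The windows differ, so the mirroring is imperfect, but a spurious self-report result could be set against its registry counterpart. Respiratory symptoms has no such check.
- The scenarios are constructed. Bias needs response to depend on the outcome differently by arm; low response, unequal response, or illness-related non-response shared by both arms does not produce it when there is no true effect. Nothing in the protocol supports a gap of 10 or 20 percentage points.
- Follow-up is not neglected. The absence of contact concerns adherence during the two weeks; an e-mail and up to two reminders follow.
- The remedy is partial. Imputation or weighting assumes that response is unrelated to the outcome once registry data are known, whereas the scenarios above let it depend on the unregistered outcome itself. No missing-data method corrects open-label reporting, that is, participants describing symptoms differently because they know their arm.

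A reader might also infer that leaving missing data unhandled contradicts the intention-to-treat commitment. It does not: the protocol defines that principle as analysis by allocated group and applies it to the data collected. It nowhere claims that questionnaire outcomes will cover everyone randomised.

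None of this answers the central point. The protocol rules out a better analysis for which it is already collecting the data.

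**Conclusion.** The point holds as an avoidable weakness in the analysis of five secondary outcomes. The illustrative relative risks of 0.88 and 0.75 show how far response behaviour alone could move the result at 2% risk; they rest on assumed response rates and on a difference between arms in event-related non-response.

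Because 0.75 matches the trial's target effect, a reader might infer that non-response is likely to manufacture the trial's finding. The documents do not support that. The registry primary outcome does not depend on the questionnaire, no response rate is given, and other equally simple patterns of non-response give exactly 1.00. What is shown is a risk, not a demonstrated bias. It is greatest for respiratory symptoms and should be dealt with before the data are analysed.

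**What to change.** Replace the missing-data sentence with text such as:

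> Questionnaire outcomes will be analysed in all randomised participants who have not withdrawn, by multiple imputation within arm or by inverse-probability-of-response weighting, using age, sex, vaccination status, tests before the study, MSIS result and KPR/NPR contacts. Responders-only relative risks will be shown alongside, with response rates by arm. For self-reported positive test and respiratory symptoms, a delta-adjusted sensitivity analysis will vary the assumed risk in non-responders, separately by arm.

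Choose one of the two methods in advance. The section on statistical methods for primary and secondary outcomes must be reconciled too, since it commits all prespecified outcomes to unadjusted analysis. It could keep that for the registry outcomes and refer to the new text for the questionnaire outcomes.

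No new data collection is needed. The cost is prespecifying an imputation or weighting model and a range for the sensitivity analysis. The limit should be stated openly: the method removes bias only as far as the registries capture the outcome, which is least for respiratory symptoms.

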#### **Plans to give access to the full protocol, participant level-data and statistical code**

We intend to give full access to the full protocol, participant-level dataset, and statistical code, to anyone who is interested, after securing that the dataset is fully anonymized.

## **Oversight**

#### **Adverse event reporting and harm**

We will ask the participants whether they needed any medical attention during the trial period, and specifically ask for injuries.

#### **Plans for communicating important protocol amendments to relevant parties (e.g. trial participants, ethical committees)**

We will report important protocol modifications (e.g., changes to eligibility criteria, outcomes, analyses) to the Regional Ethics Committee.

#### **Dissemination plans**

We plan to communicate trial results to the public, and other relevant groups via publication in peer-reviewed biomedical journals, via social media, and through the Norwegian Institute of Public Health website.

## **Trial status**

The trial is planned to commence Feb 2nd, 2022.

#### **Funding**

All running costs are covered by the Norwegian Institute of Public Health.

#### **Availability of data and materials**

The final anonymized trial dataset will be freely available to the public.

## Competing interests

The authors declare that they have no competing interests.

